**Randomization**

Randomization is carried out at the INCL inclusion visit, after verification of inclusion / non-inclusion criteria. Treatments are randomized with a 1:1 allocation for both treatments. Randomization will be stratified by center (n = 5) and the draw will be made in chronological order of arrival of patients, from randomization lists drawn up by the Rouen University Hospital Biostatistics Service ([name]). These lists provide the randomization codes corresponding to treatment batch numbers.

These randomization lists will subsequently be forwarded to the service provider (Company LC2) who will prepare sealed envelopes, box therapeutic units, and produce unblinding envelopes for each center.

At each inclusion a processing number will be assigned to each patient. The treatment can then be issued by the central pharmacy at each center so that treatment can commence the following day.

**Double blind**

The treatment period in parallel groups is double-blinded. The blind will be maintained until final data analysis.

The treatment code (type of treatment) assigned to each patient will be kept by the sponsor, by the main investigator and by the central pharmacy at each center in sealed envelopes.

In cases where unblinding is needed, i.e. in the event of severe adverse events requiring knowledge of the assigned treatment for patient care, the investigator should first try to contact the trial coordinating investigator before disclosure of the treatment code.

If an envelope is opened, the reason, the opening date and the signature of the investigator should be noted on it. At the end of the study, during the final visit, all envelopes (sealed and opened) will be collected and returned to the promoter.

III.4.3 Tracking information and study products

Treatment distribution will be carried out by the Company LC2, Packaging and Logistics Laboratory for clinical batches (Lentilly 69210).

The numbered batches will be distributed to different centers. Each batch will initially include six weeks of treatment to minimize costs. Should this treatment time prove insufficient, another batch will be given to the patient. Each patient will receive a placebo, or the Adalate LP 20 mg ® in tablet form.

III.4.4 Treatment procedure

All patients will initially be hospitalized for at least 48 hours to monitor the extent of bleeding and assess hemodynamic status (normal standard blood test in this context includes CBC, PT, APTT, antiglobulin testing, blood pressure monitoring every 6 hours).

All patients initially receive tocolysis with nifedipine or tractocile for 48 hours: 1 capsule of nifedipine (Adalate®) 10 mg by oral route renewable every 20 minutes up to 4 capsules per hour, followed by long-acting nifedipine for 48 hours (Adalate LP 20mg®, one 20 mg tablet, 3 times daily) or tractotile (Atosiban®).

All patients initially receive an injection of Célèstène chronodose® 12 mg in a single intramuscular injection, 2 consecutive days.

All patients will receive preventive iron therapy: 80mg Tardyferon ®, 2 tablets and 5mg Spéciafoldine ®, 1 tablet daily.

**The following treatment protocol** will then be offered to patients after the first 48 hours of hospitalization. The protocol will commence only after validation of inclusion / non-inclusion criteria and reception of patient consent.

After randomization, a treatment batch will be given to the patient. Each batch will initially include treatment for six weeks to minimise costs. Should this length of time prove insufficient, another batch will then given to the patient. Depending on randomization, tablets for a given patient will be:

- Group A = Placebo

- Group B = Adalate LP 20mg ®

All patients will take 3 tablets daily, 1 tablet morning, noon and night.

The treatment will be continued without interruption until 36 weeks + 6 days.

Patients will be able to return home after the first bleeding episode if there is complete resolution of the episode and if the place of residence is at a distance of less than 30 minutes by car.

In case of rebleeding or the onset of painful contractions, further tocolysis by nifedipine or tractocile can be administered for 48 hours (in compliance with the initial tocolysis previously described). Tablets taken as part of the long- term treatment will be interrupted for the duration of this tocolysis. A second and final return home is possible under the same conditions as defined above.

In order to assess evolution in location of the placenta, monitoring by endovaginal ultrasound will be performed on a monthly basis.

Clinical monitoring will be carried out bi monthly to pinpoint possible intolerance to treatment or adverse effects.

III.4.5 Prohibited concurrent therapies

Enzyme-inducing anticonvulsants, baclofen, cimetidine, itraconazole, phenytoin, rifampicin, alpha blockers, amifostine, tricyclic antidepressants, neuroleptics, beta-blockers.

III.5 Visits et Evaluation

III 5.1 Trial procedure

Group 1: Placebo

Group 2: Adalate LP 20mg ®

Treatment by Placebo or Adalate LP 20mg ®

Fortnightly monitoring

Early discharge possible

Jours – Days

Visites – Visits

SEL – Screening visit

INCL – Inclusion visit

N – Maximum period for prescription of treatment

SOR: Discharge of patient and new-born infant from the maternity unit

III.5.2 Schedule of Visits

| **Tests** | **Initial Tocolysis** | **Randomization** | **Monitoring** | **Monitoring** | **Early discharge** | **Treatment interrupted** | **End** |
| --- | --- | --- | --- | --- | --- | --- | --- |
| Days | -1 | 0 | / 15 | / 30 | N - | N | N + |
| Visits | SEL | INCL | SURV 15 | SURV 30 | PREM | 36 WA + 6 | SOR |
| Patient information  Patient consent | X |  |  |  |  |  |  |
| Inclusion criteria  Non-inclusion criteria | X | X |  |  |  |  |  |
| Demographic data | X |  |  |  |  |  |  |
| Medical antecedents  Surgical antecedents |  | X |  |  |  |  |  |
| Full pathology history |  | X |  |  |  |  |  |
| Dispensing of treatment |  | X |  |  |  |  |  |
| Patient follow-up schedule |  | X |  |  |  |  |  |
| Patient blood pressure | X | X | X | X | X | X | X |
| Patient blood tests :  CBC / PT / APTT / antiglobulin | X |  |  |  |  |  | X |
| Endovaginal echography |  |  |  | X |  |  |  |
| Adherence to treatment |  |  | X | X | X | X | X |
| Overall tolerance to treatment  Satisfaction with treatment |  |  | X | X | X | X | X |
| Maternal data at trial completion  (See page 13 : Final visit) |  |  |  |  |  |  | X |
| Neonatal data at trial completion  (See page 13 : Final visit) |  |  |  |  |  |  | X |
| Effets / undesirable events |  | X | X | X | X | X | X |
| Concurrent treatment | X | X | X | X | X | X | X |

11

III.5.3. Visits schedule

**Screening visit : SEL visit (J-1)**

Evaluations are presented in Table III.5.2.

1. Verification of inclusion / non-inclusion criteria.

2. Obtain informed consent form signed by the patient.

3. Obtain history of the disease, past major medical and surgical history, and associated treatments.

**Inclusion Visit / Randomization and Start of treatment: Visit INCL (J 0)**

Randomization is performed after checking of inclusion / non-inclusion criteria. Treatments are randomized with a 1:1 allocation for both treatments.

Randomized patients will take their first tablet, Placebo or Adalate LP 20mg ®, the day after the INCL visit (J 0).

1. Verification of inclusion / non-inclusion criteria.

2. Take in the informed consent form signed by the patient.

3. Randomization.

4. Allocate patient treatment.

5. Plan a monitoring schedule with the patient.

6. Go through the adverse effects.

**Intermediate monitoring visits**

Evaluations as presented in Table III.5.2.

1. Look for possible allergy, flushing, symptomatic hypotension, headaches.

2. Blood pressure monitoring.

**Re- hospitalization**

In cases of bleeding recurrence

In cases of adverse effects.

**Treatment discontinuation no later than 36 weeks + 6 days**

Evaluations as presented in Table III.5.2.

**Final visit before discharge of mother and child from maternity unit**

For the mother:

1. blood count

2. treatment satisfaction

3. transfusion or prescribing of Venofer

4. Data collection concerning delivery and complications linked to immediate postpartum period.

For the child:

1. blood sample from cord at birth (placenta)

2. term at birth

3. birth weight,

4. length of hospitalization,

5. neonatal morbidity.

III.5.4 Assessment of effectiveness of treatment

**Primary efficacy parameters**

• **Significant prolongation of pregnancy**: time elapsed from the start of treatment to delivery are compared in each group.

**Secondary efficacy parameters**

• **Improved maternal prognosis:**  the two groups are compared as follows;

- Delta hemoglobin level at inclusion and in the immediate postpartum period,

- The need for transfusion or prescription of Venofer.

• **Improved neonatal prognosis:** the two groups are compared as follows;

- Birth weight,

- Term at birth,

- length of hospitalization,

- Morbidity, mortality.

III.5.5 Assessment of tolerance

**Assessment is carried out through questioning and by taking patient blood pressure at the various visits planned in the protocol.**

III.5.6 Assessment of compliance

Adherence to the study will be assessed by:

- Questioning of the patient at each follow-up visit,

- A count of the treatment units remaining and used (empty packaging) brought by the patient and relating to the 15 day period leading up to each follow-up visit.

III.6 Endpoints

III.6.1 Primary endpoint

The primary endpoint will be the duration in days of the prolongation of pregnancy from the initial bleeding episode.

III.6.2 Secondary Endpoints

Assessment criteria for secondary maternal endpoints will be:

- pregnancy prolongation beyond 15 days following the initial bleed,

- frequency of rebleeding,

- side effects of treatments,

- need for transfusion or the prescription of Venofer,

- emergency and hemorrhagic caesarean section,

- hemoglobin levels immediately before birth and in the immediate postpartum period,

- need for a hemostatic hysterectomy or embolization,

- Postpartum hospital stay,

- Maternal mortality.

Assessment criteria for neonatal secondary outcomes will be:

- birth weight,

- Apgar score at 5 minutes,

- arterial pH at birth,

- hemoglobin count taken from newborn cord

- hospitalization in intensive care unit

- length of hospitalization,

- Neonatal morbidity associated with prematurity

- Neonatal and perinatal mortality.

IV. Trial Drop-out

The following circumstances will be considered as sufficient to opt for early discontinuation:

1. Likely intolerance to treatment: e.g. persistent headache, flushing, maternal hypotension.

2. Discontinuation of treatment.

3. Occurrence of heavy bleeding or abnormal fetal heart rate justifying rapid termination of pregnancy.

4. Premature rupture of membranes during treatment.

5. In cases where additional maternal pathology justify a termination of pregnancy.

6. If ultrasound monitoring reveals a distance between the lower part of the placenta and the internal cervical os greater than 5 cm.

Any patient leaving the study due to an adverse event should be followed up until resolution of the adverse event.

In cases of early drop-out from the trial, the final observation report forms should be completed.

V. Statistical methods

V.1 Calculation of patient numbers

The patient number calculation is based on the duration of the prolongation of pregnancy from the initial bleeding episode (primary endpoint). The average length of prolongation of pregnancy and standard deviations used are derived from data published by Bessinger RE et al. To highlight a difference in mean length of prolongation of pregnancy of 14 days between the two groups (15 days average prolongation in the short tocolysis group versus 40 days in the extended tocolysis group) with a standard deviation of 25 days, 52 subjects are required per group with a power of 80% and a p-value of 5% (bilateral formulation). This number also allows at a power of 80% to detect a 26.5% difference in percentage of women for whom the prolongation of pregnancy will be longer than 14 days (50% for short tocolysis versus 76.5% for extended tocolysis).

V.2 Statistical Analysis

Comparisons of the two groups will be based on intention to treat analysis. For the primary endpoint, both groups will first be compared by means of the Student t-test and secondly by a linear regression model taking into account potential prognostic factors (type of placenta previa and gestational age at inclusion). The same type of analysis will be carried out for other quantitative variables. For binary criteria, the comparison between the two groups will be made using the Chi 2 test or the Fisher exact test if necessary, complemented by a logistic regression test to take into account other prognostic factors.

V.3 Feasibility Study

Four of the participating centers are level 4 maternity hospitals with neonatal intensive care units and one is a level 2B maternity hospital with a neonatology department. These centers, due to their structure, are able to manage placenta previa bleeding in clinical practice. The total number patients treated for placenta previa or low-lying placenta is on average 20 per year at Rouen University Hospital, half of the total patient numbers (see below).

The duration of the trial shall be 2 years.

VI. Bibliography

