The expected risks would be associated with a prolonged administration of nifedipine, as all other patient care follows current standard practice. Adverse effects of calcium channel blockers are usually very mild and only rarely require stopping treatment. These adverse effects usually occur at the start of treatment, essentially in the form of headaches and transient flushing. Arterial hypotension in non-hypertensive pregnant women is rare. The Cochrane Database meta-analysis report no cases of symptomatic hypotension warranting cessation of treatment (5). The expected significant risk to the mother may be the appearance of an allergic reaction justifying an immediate interruption of treatment and leaving the protocol.

A fetotoxic effect of calcium channel blockers has been reported in animals. This effect has never been reported in humans (Vidal dictionary). The Cochrane Database meta-analysis reports no cause to suggest possible toxicity linked to calcium channel blockers. The analysis however reports lower neonatal morbidity when using calcium channel blockers compared to beta-agonists.

II. Study Objectives

The objective of this study is to determine whether extended tocolysis with a calcium inhibitor may improve maternal or fetal prognosis in cases of low-lying hemorrhagic placenta.

II.1 Main objective

The main objective of this study is to assess the benefits of extended tocolysis with a calcium inhibitor on the duration of prolongation of pregnancy from the initial bleeding episode.

II.2 Secondary Objectives

- To evaluate the side effects of nifedipine treatment in cases of extended tocolysis.

- To evaluate a possible reduction in maternal blood loss in cases of extended tocolysis while assessing the need or not for transfusion or interventional hemostasis techniques.

- To evaluate possible improvement in neonatal prognosis in cases of extended tocolysis while assessing term at birth, birth weight and immediate neonatal morbidity.

III. Study Design

III.1 Methodology

This is a prospective, therapeutic, multicentered (5 centers), double-blinded randomized, study. Any patient pregnant for a minimum of 24 WK, hospitalized for bleeding placenta previa will initially receive short-term tocolysis by calcium inhibitor or oxytocin inhibitor for 48 hours in order to establish maturation by corticosteroids. After the 48 hours, patients wishing to participate in the study will be randomized.

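### The haemoglobin secondary endpoint is stated in two unreconciled ways, and one of them needs a pre-birth count that the visit schedule does not provide

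*Protocol*

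**What the plan says.** Two sections of the protocol define the maternal haemoglobin comparison.

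- III.5.4, under the secondary efficacy parameters: "Delta hemoglobin level at inclusion and in the immediate postpartum period".
- III.6.2, under the maternal secondary endpoints: "hemoglobin levels immediately before birth and in the immediate postpartum period".

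The schedule in III.5.2 has the visit columns "SEL | INCL | SURV 15 | SURV 30 | PREM | 36 WA + 6 | SOR", with no column for delivery. Its row for maternal blood tests ("CBC / PT / APTT / antiglobulin") is marked in the first column (SEL, day -1) and the last (SOR), and is blank at INCL, both monitoring visits, PREM and 36 WA + 6. The legend gives "SOR: Discharge of patient and new-born infant from the maternity unit". The visit descriptions in III.5.3 list a maternal blood count once, under "Final visit before discharge of mother and child from maternity unit". III.4.4 adds that the work-up during the first hospital stay ("normal standard blood test in this context includes CBC, PT, APTT, antiglobulin testing") contains a blood count, which is before randomization.

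II.2 states the blood-loss objective and ties it to "assessing the need or not for transfusion or interventional hemostasis techniques". V.2 prescribes a t-test followed by a linear regression on type of placenta previa and gestational age at inclusion, and extends the same approach to the other quantitative variables. Baseline haemoglobin is not among the named covariates.

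**The concern.** A reader of III.5.4 and a reader of III.6.2 would compute different things. The protocol does not say which is the haemoglobin endpoint, or whether both are. If this is left open, two results could be reported under the same label and the choice made after the data are seen.

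The III.6.2 version also depends on a count that no visit provides for. It could be missing for many women, and missing unevenly, for example by centre or by urgency of delivery. The III.5.4 version can be computed only by taking SEL as inclusion and the pre-discharge count as immediate postpartum, and neither substitution is written down.

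Finally, a raw change is a noisy way to use a baseline value that is already collected. V.2 fixes the covariates for quantitative variables without naming that baseline.

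**Working it through.** **Step 1. Set the sections side by side.**

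| Element | III.5.4 | III.6.2 | Count available under III.5.2 and III.5.3 |
|---|---|---|---|
| First time point | Inclusion | Just before birth | SEL (day -1); none at INCL; none before birth |
| Second time point | Immediate postpartum | Immediate postpartum | SOR, before discharge |
| Form | Change | Levels | Not applicable |

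The second time point agrees between the two definitions. The first time point and the form do not. Of the three time points named, inclusion and postpartum have an approximate scheduled source; the pre-birth one has none.

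**Step 2. Is there a stated figure to reproduce?** No. The protocol gives no standard deviation, effect or power for the haemoglobin endpoint. The sample size in V.1 is built on prolongation of pregnancy and does not bear on this point.

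**Step 3. Raw change against baseline-adjusted level.** Let σ² be the within-arm variance of haemoglobin, assumed equal at SEL and SOR, and ρ the correlation between the two counts. The protocol gives no value of ρ, so 0.3 and 0.5 are assumptions.

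- Variance of the raw change: 2σ²(1 − ρ)
- Residual variance of SOR haemoglobin adjusted for SEL: σ²(1 − ρ²)
- Ratio: (1 − ρ²) / [2(1 − ρ)] = (1 + ρ)/2

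| ρ | Raw change | Adjusted | Ratio | Reduction |
|---|---|---|---|---|
| 0.3 | 1.40σ² | 0.91σ² | 0.65 | 35% |
| 0.5 | 1.00σ² | 0.75σ² | 0.75 | 25% |

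**Step 4. The same in haemoglobin units, as an illustration.** The small randomized ritodrine study described in I.2 reports standard deviations of 1.3 and 1.2 g/100 ml after one week of treatment. Assume these apply here. With 52 per arm, 80% power and two-sided 5%, the detectable difference in an unadjusted level is 2.80 × SD × √(2/52), which is 0.66 for SD 1.2 and 0.71 for SD 1.3. Multiplying by the square root of the variance factors in step 3 gives:

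| ρ | Raw change (SD 1.2 / 1.3) | Adjusted (SD 1.2 / 1.3) |
|---|---|---|
| 0.3 | 0.78 / 0.85 | 0.63 / 0.68 |
| 0.5 | 0.66 / 0.71 | 0.57 / 0.62 |

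The gain is roughly 0.1 to 0.2 g/100 ml in detectable difference. It says nothing about how often the pre-birth count would be missing, which cannot be estimated from the protocol.

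**The case against.** The strongest reply is that the two definitions are complementary. III.6.2 lists levels and does not ask for a subtraction. A pre-birth level compared between randomized arms would reflect bleeding before delivery, which is what extended tocolysis is meant to reduce. Both measures could be reported if the sample had a source. This stands: the definitions are unreconciled rather than incompatible, and the pre-birth level should not be discarded.

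A second reply is that the lack of a delivery column does not prove that no count exists. III.5.3 collects cord blood and delivery data under the final visit, so a delivery-time maternal value might be gathered in the same way. This stands in part. The protocol is silent on such a count, so the fair statement is that its source is not specified.

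A third is that covariates and the handling of transfusion belong in the statistical analysis plan, which is not shown. For transfusion this stands: transfusion or Venofer is compared separately in both sections, so its influence would be visible, and no particular sensitivity analysis is owed here. For the covariate it stands less well, because V.2 already names the adjustment factors and III.5.4 already names a change. The two definitions are both in the protocol itself.

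A reader might go further and infer that the blood-loss objective is assessed over the wrong interval, or cannot be assessed. The protocol does not support that. II.2 does not name haemoglobin; the transfusion and haemostasis endpoints in III.6.2 do not depend on these samples. The III.5.4 change spans the treatment period and can be approximated from SEL and SOR.

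**Conclusion.** The point holds as a minor inconsistency in one secondary endpoint. III.5.4 and III.6.2 differ in first time point and in form, III.5.2 provides no source for the pre-birth value, and the named inclusion and postpartum values can only be the SEL and pre-discharge SOR counts. The blood-loss objective, the primary endpoint and the sample size are unaffected.

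The quantified part is the gain from replacing the raw change with a baseline-adjusted comparison: 35% lower variance at a correlation of 0.3 and 25% at 0.5. This rests on equal variances at the two times and on assumed correlations. The figures in g/100 ml rest further on standard deviations borrowed from another study.

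**What to change.** Use one definition in III.5.4 and III.6.2: postpartum haemoglobin at SOR, compared between arms by the V.2 linear regression with SEL haemoglobin added to the two covariates already named, in place of the raw change. State in both sections that SEL supplies the baseline and SOR the postpartum value.

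Keep the pre-birth level as a descriptive measure where a count is available, state where that count comes from, and report how many women have one. Present the haemoglobin result next to the transfusion/Venofer endpoint, because both treatments raise the SOR value.

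**Cost:** an amendment of wording in III.5.4, III.6.2 and V.2, with no new samples. **Downside:** the SOR count is taken before discharge, so its timing varies with length of stay and it follows any in-stay transfusion or iron. Adjusting for SEL haemoglobin does not remove that.
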